### 8.3.3. ECOG Performance Status

The Eastern Cooperative Oncology Group Performance Status (PS).

Assessed at baseline and after 4 and 12 weeks of follow-up

### 8.3.4. Clinical Safety Laboratory Assessments

Study-specific clinical safety laboratory assessments will not be performed. Relevant tests will be decided and acted on by the local clinical oncologist and will depend on the medical condition of individual patients. Such tests will not be recorded in the eCRF unless relevant for the reporting of AEs/SAEs.

Study-specific laboratory assessment included in prognostic scores (CRP, LDH, albumin, hemoglobin and platelets) will be performed ([Section 8.4.1](#)).

### 8.3.5. Pregnancy Testing

- To be performed before randomization of WOCBP. A woman is considered being of childbearing potential, i.e. fertile, following menarche and until becoming postmenopausal unless permanently sterile (due to hysterectomy, bilateral salpingectomy and bilateral oophorectomy), or considered infertile due to earlier cancer treatment.
- Due to the short intervention time, pregnancy testing will not be repeated during the study period.
- WOCBP must consent to the use of highly effective methods for birth control, be surgically sterile ([Appendix 10.4](#)) or abstain from heterosexual activity from randomization until completed study intervention ([Section 5.1](#))

## 8.4. Other Assessments

### 8.4.1. Baseline Prognostic Scores

As an exploratory objective, the prognostic impact of GPS (23, 78), LabBM score (25, 79) and LabPS-score (24) will be assessed at baseline (maximum 4 weeks prior to start of radiotherapy). The scores include the following parameters:

|       |                                                                      |
|-------|----------------------------------------------------------------------|
| GPS   | CRP, albumin                                                         |
| LabBM | CRP, albumin, LDH, hemoglobin, platelets                             |
| LabPS | CRP, albumin, LDH, hemoglobin, platelets and ECOG Performance Status |

#### **8.4.2. Predictive Biomarkers**

Analyses will be performed on MRI and tumor biopsies available from standard diagnostic work-up and follow-up. There will not be performed study-specific procedures, hence, the analyses will be performed in subgroups of patients depending on availability of examinations.

##### Functional MRI

MRI with functional DW (diffusion-weighted) and/or DCE (dynamic contrast-enhanced) sequences will be analyzed using the Consumption and Supply-based Hypoxia (CSH)-imaging method (27, 66, 80). The hypoxia images will determine the number of voxels located in hypoxic areas within the defined tumor, and the hypoxic fraction (HF) will be assessed.

In addition, available MRI sequences will be explored to obtain tumor information of potential prognostic and/or predictive value.

##### Molecular Analyses on Tumor Biopsies

Tumor ribonucleic acid (RNA) will be isolated from paraffin-embedded tissue blocks and subjected to global gene expression analysis using the QuantSeq RNA-sequencing method or NanoString technology. These technologies are robust and appropriate for analyses of RNA from paraffin embedded material. The gene expression data will be used to indicate hypoxia by using previously established signatures like the Ragnum signature (67) and the signature by Fjeldbo et al (81, 82). A score will be calculated from the expression levels of the signature genes in the tumor and used in the analyses.

The expression data of all genes in the genome will further be used for explorative analyses to obtain information about signaling pathways that are activated in the tumors. Protein expression will be measured for selected genes by immunohistochemistry based on the paraffin-embedded tissue blocks

PD-L1 expression will be assessed on paraffin-embedded tissue blocks by immunohistochemical staining, and the CPS score will be calculated.

##### CB-CT

CB-CT acquired during radiotherapy for control of positioning will be explored for evaluation of tumor response and technical aspects of delivered radiotherapy

#### **8.5. Adverse Events (AEs), Serious Adverse Events (SAEs), and Other Safety Reporting**

The definitions of AEs and SAEs can be found in [Appendix 3](#). AEs will be reported by the patients, by a caregiver, surrogate, or the patient's legally authorized representative (when appropriate).

The investigators and any qualified designees are responsible for detecting, documenting, and recording events that meet the definition of an AE or SAE and remain responsible for following up all AEs that are serious, considered related to the study intervention, or caused the patient to discontinue the study intervention ([see Section 7](#)).

The method of recording, evaluating, and assessing causality of AEs and SAEs and the procedures for completing and transmitting SAE reports are provided in [Appendix 3](#).

#### **8.5.1. Time Period and Frequency of Collecting AE and SAE Information**

All SAEs and AEs with CTCAE grade  $\geq 3$  will be collected from the start of study intervention until the 52 week follow-up visit as specified in the SoA ([Section 1.2](#)), and recorded in the eCRF. After the 4 week follow-up visit, only SAEs/AEs with CTCAE grade  $\geq 3$  with probable/definite causality with radiotherapy will be reported. For patients in arm A receiving a second radiotherapy fraction, all SAEs/AEs with CTCAE grade  $\geq 3$  will be reported until the 8 week follow-up.

Medical occurrences that begin before the start of study intervention, but after obtaining informed consent will be recorded as current medical history ([section 8.1](#)), and not as AEs.

All SAEs will be recorded and reported to the sponsor or designee immediately and under no circumstance should this exceed 24 hours, as indicated in [Appendix 3](#). The investigator will submit any updated SAE data to the sponsor within 24 hours of it being available.

Investigators are not obligated to actively seek information on AEs or SAEs after conclusion of the study participation. However, if the investigator learns of any SAE, including a death, at any time after a patient has been discharged from the study, and he/she considers the event to be reasonably related to the study intervention or study participation, the investigator must promptly notify the sponsor.

#### **8.5.2. Method of Detecting AEs and SAEs**

Patients will be instructed to contact their investigator/designated staff at any time after consenting to participate in the study if any symptoms develop. In addition, information on AEs and SAEs will be collected at predefined time points as specified in the SoA ([Section 1.2](#)). Care will be taken not to introduce bias when detecting AEs and/or SAEs. Open-ended and non-leading verbal questioning of the patient is the preferred method to inquire about AE occurrences.

#### **8.5.3. Follow-up of AEs and SAEs**

After the initial AE/SAE report, the investigator is required to proactively follow each patient at subsequent visits/contacts. All SAEs considered related to the study intervention, or that caused the patient to discontinue the study intervention, will be followed until resolution, stabilization,

the event is otherwise explained, or the patient is lost to follow-up (as defined in [Section 7.3](#). Further information on follow-up procedures is provided in [Appendix 10.3](#).

In the case of a serious AE/SAE, the investigator should initiate the appropriate treatment according to their medical judgement.

Treatment of AEs/SAEs shall not be recorded in the eCRF, only the intensity, causality and outcome see [Appendix 10.3](#).

#### **8.5.4. Regulatory Reporting Requirements for SAEs**

- Prompt notification by the investigator to the sponsor of an SAE is essential so that legal obligations and ethical responsibilities towards the safety of patients and the safety of a study intervention under clinical investigation are met.
- The sponsor has a legal responsibility to notify both the local regulatory authority and other regulatory agencies about the safety of a study intervention under clinical investigation. The sponsor will comply with country-specific regulatory requirements relating to safety reporting to the regulatory authority, Institutional Review Boards (IRB)/Independent Ethics Committees (IEC), and investigators.

#### **8.5.5. Pregnancy**

- Patients with a positive pregnancy test will not be included due to risk of teratogenic and abortifacient effects of radiotherapy ([Section 5.2](#)).
- WOCBP must consent to the use of effective birth control ([Appendix 10.4](#)) or abstain from heterosexual activity from randomization and until completed study intervention ([Section 5.1](#))

#### **8.5.6. Disease-Related Events and/or Disease-Related Outcomes Not Qualifying as AEs or SAEs**

The following disease-related events are common in patients with metastatic malignant disease and can be serious/life-threatening:

- Event A: hospitalization or death due to disease progression
- Event B: hospitalization for planned investigations or blood/platelet transfusions/fluid transfusions
- Event C: hospitalization for febrile neutropenia if chemotherapy is administered 8-21 days before start of radiotherapy (systemic treatment must be paused one week prior to, during and one week after study intervention)
- Event D: hospitalization for palliative or terminal care

Because these events are typically associated with the disease under study, they will not be reported according to the standard process for expedited reporting of SAEs even though the event may meet the definition of an SAE.

NOTE: However, if either of the following conditions applies, then the event must be recorded and reported as an AE/SAE (instead of a disease-related event):

The event is, in the investigator's opinion, of greater intensity, frequency, or duration than expected for the individual patient.

OR

The investigator considers that there is a reasonable possibility that the event is related to study intervention.

## **8.6. Pharmacokinetics**

Pharmacokinetic parameters will not be evaluated in this study.

## **8.7. Genetics and/or Pharmacogenomics**

Genetics/pharmacogenomics will not be evaluated in this study.

## **8.8. Biomarkers**

Blood test will be collected for assessment of prognostic scores (GPS, LabBM and LabPS), [Section 8.4.1](#). Predictive biomarkers based on medical images and biopsies will be assessed when available, se [section 8.4.2](#).

## **8.9. Immunogenicity Assessments**

Not applicable

## **8.10. Health Economics OR Medical Resource Utilization and Health Economics**

Health economics will be evaluated as indicated in [section 8.2.3](#).

## **9. Statistical Considerations**

### **9.1. Choice of Non-inferiority Margin**

The non-inferiority margin of the difference in the primary endpoint (change in target symptom intensity from baseline after 12 weeks of follow-up) between the two study arms is set to 1 point, which is 50% of the considered minimum clinically important difference based on clinical trials investigating cancer pain (83). The same non-inferiority margin is also currently applied in an ongoing clinical non-inferiority trial (PARASTOP) investigating cancer pain (ClinicalTrials.gov registry number: NCT 05051735). To our judgement, given a different in target symptom relief of less than 1 point, clinicians would prefer radiotherapy with 1-2 fractions of 8 Gy over five fractions of 5 Gy.

### **9.2. Statistical Hypotheses**

The primary hypothesis is that a radiotherapy schedule of 1-2 fractions of 8 Gy provides non-inferior patient-reported symptomatic relief as a schedule of five fractions of 5, assessed 12 weeks after completed radiotherapy (see [Section 9.1](#) for definition of the non-inferiority margin). The lower bound of the 95% confidence interval of the difference in mean symptom intensity of arm A is therefore hypothesized to be above the non-inferiority margin of -1.

If non-inferiority regarding symptom relief, and comparable QoL, toxicities and OS can be proved 12 weeks after the intervention a short-course schedule with 1-2 fractions will be recommend as standard of care. If non-inferiority can be proven only 4 weeks after the intervention, a single fraction schedule will be recommend for patients with a very short life expectancy where palliative radiotherapy is considered reasonable.

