### **2.2.2.4. Gynecological Cancer**

In an observational, retrospective study from 1986, Halle et al. studied the effect of a single fraction of 10 Gy to the pelvis in advanced cancers of the cervix or endometrium (73). The fraction was repeated once or twice at monthly intervals when necessary. The study reported acceptable symptomatic response, but serious side effects were observed in patients surviving more than approximately one year. The authors therefore concluded that 10 Gy fractions should be limited to patients with a life expectancy of less than 12 months.

A similar retrospective Norwegian study, also employing a schedule with one single 10 Gy fraction, was conducted in 2001, and included patients with a life expectancy of less than 12 months (74). However, 28 % of the patients survived beyond 12 months, demonstrating the challenge with lifetime predictions. The study reported a good response on bleeding and vaginal discharge, but serious bowel complications occurred from 9 months onward after radiotherapy.

In a more recent, retrospective study from 2011, another regimen with a single fraction of 8 Gy, repeated at day 7 and 21 if feasible and necessary, was used (75). The study reported effective and rapid symptomatic responses with acceptable toxicity.

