#### **Secondary objective**

*To assess the efficacy of 1-2 fractions of 8 Gy compared to 5 fractions of 5 Gy with respect to:*

- Physician-reported toxicities

Endpoint: Bladder and bowel toxicity after 4, 12 and 52 weeks of follow-up

Assessment: Common Terminology Criteria for Adverse Events (CTCAE) v 5.0

- Survival

Endpoint: Overall survival (OS) assessed at the end of study

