**Figure 1: Study timeline**

## 4.2. Scientific Rationale for Study Design

The principal research question is whether a short-course radiotherapy schedule of 1-2 fractions provide non-inferior patient-reported symptom relief compared to a schedule of 5 fractions, assessed 12 weeks after completed radiotherapy. If non-inferiority is established, and general QoL, toxicities and overall survival are comparable between the two study arms, a short-course schedule will be preferred, as it will be less burdensome for patients and provide improved exploitation of health care resources. A superiority study would therefore not be necessary in order to implement treatment results. Although superiority studies that fail to reject the null hypothesis are frequently interpreted as showing no differences between groups, they should be interpreted as indeterminate (77).

If non-inferiority can be proved only 4 weeks after completed radiotherapy, a single fraction schedule will be recommend for patients with a very short life expectancy for whom palliative radiotherapy is considered reasonable.

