#### **4.4. End of Study Definition**

The end of study is defined as the last patient last visit (LPLV), i.e. the data when the last patient complete the study. A patient is considered to have completed the study if he/she has completed all phases of the study including the last visit at 52 weeks.

The study may be terminated by the investigators, trial steering committee and/or sponsor for clinical or administrative reasons.

The end of study will be reported to the Regulatory Authority and institutional review boards (IRB)/independent ethics committee (IEC) within 90 days, or 15 days if the study is terminated prematurely. The investigators will inform included patients of the premature end of study and ensure that appropriate follow-up is arranged for all patients involved

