### **8.2.2. Overall Survival**

Will be assessed at the end of the study defined as LPLV.

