#### **9.5.4. Exploratory endpoints**

Analyses of exploratory endpoints will be regarded as hypothesis-generating post-hoc analyses. Continuous endpoints will typically be analyzed by linear regression or median regression, as appropriate. Dichotomous endpoints will typically be analyzed by logistic regression.

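### Section 9.2 lets the standard-of-care recommendation rest on toxicity and survival at 12 weeks, although survival is defined only at the end of study and toxicity also at 52 weeks

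*Protocol*

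**What the plan says.** Section 9.2 first states the primary non-inferiority hypothesis on symptom relief at 12 weeks. It then gives the condition for making the short course standard of care: with non-inferior symptom relief, if "comparable QoL, toxicities and OS can be proved 12 weeks after the intervention a short-course schedule with 1-2 fractions will be recommend".

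The endpoints named in that rule are defined elsewhere:

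- Toxicity (section 3, secondary objective): "Endpoint: Bladder and bowel toxicity after 4, 12 and 52 weeks of follow-up". Section 9.4 gives each of the three time points its own analysis set; the 52-week analysis uses the per-protocol set.
- Survival (section 3): "Endpoint: Overall survival (OS) assessed at the end of study". Section 8.2.2 repeats this: "Will be assessed at the end of the study defined as LPLV". Under section 4.4 a patient has completed the study after having "completed all phases of the study including the last visit at 52 weeks".
- Quality of life (section 3, exploratory): 4, 8, 12 and 26 weeks.

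Sections 2.1 and 4.2 state the same recommendation, also conditional on comparable quality of life, toxicity and OS, but attach no week to those three conditions.

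**The concern.** The 9.2 rule governs the claim that would change practice, and its time point does not match the endpoints it relies on. For OS this is a direct conflict, because the protocol defines no 12-week survival endpoint. For toxicity it is an omission: the rule can be met without the planned 52-week result.

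That result matters because of the protocol's own background. Section 2.2.2.4 reports, for a cited study of a single 10 Gy fraction, that "serious bowel complications occurred from 9 months onward after radiotherapy". A toxicity comparison that stops at 12 weeks cannot address effects of that kind. A survival comparison that stops there would rest on few deaths, and a non-significant test would say little. Section 4.2 makes this general point itself: superiority studies that fail to reject are "frequently interpreted as showing no differences between groups, they should be interpreted as indeterminate".

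**Working it through.** **The plan's own figure.** The sample size is sound and not at issue. With SD 2, margin 1, one-sided 2.5% and 85% power, n per arm = 2 × 2² × (1.960 + 1.036)² / 1² = 71.8, so 72 (144 in total). With the exact t distribution, 73 per arm (146) gives 85.1% power. Allowing 25% exclusion, 146 / 0.75 = 195, which the protocol rounds up to 200.

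**Side by side.**

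| Condition | Week in 9.2 | Week in the endpoint definition | Week in 2.1 and 4.2 |
|---|---|---|---|
| Toxicity | 12 | 4, 12, 52 | none |
| OS | 12 | end of study (LPLV) | none |
| Quality of life | 12 | 4, 8, 12, 26 | none |

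Only the OS row is a strict contradiction. In the toxicity row, 12 weeks is valid but incomplete.

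**Survival inputs.** The protocol states no survival assumption for this trial. I use the two medians it cites, 9 months (rectal, section 2.2.2.2) and 20 months (prostate, section 2.2.2.3), and assume exponential survival, 200 patients, 1:1 allocation and uniform accrual over the stated 2-4 years. Hazard λ = ln 2 / median.

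**Reading A: 12 weeks of follow-up per patient.** 12 weeks = 12/52 × 12 = 2.77 months. Share dead = 1 − exp(−λ × 2.77).

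- Median 9 months: 1 − exp(−0.213) = 19.2%, about 38 of 200.
- Median 20 months: 1 − exp(−0.096) = 9.2%, about 18 of 200.

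With D deaths split evenly, the 95% interval for the hazard ratio is the estimate multiplied and divided by exp(1.96 × 2/√D).

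- D = 38.4: factor 1.88. An observed ratio of 1.0 has interval 0.53 to 1.88.
- D = 18.3: factor 2.50. An observed ratio of 1.0 has interval 0.40 to 2.50.

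A null result would therefore be compatible with roughly a doubling of the hazard. Eligibility requires expected survival above 12 weeks, which would lower the early death count further.

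**OS as the endpoint is defined (LPLV).** With accrual a and f = 12 months after the last entry, share dead = 1 − [exp(−λf) − exp(−λ(a+f))]/(λa), for a = 24 to 48 months.

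- Median 9 months: 82-90%, 164-179 deaths, factor 1.36-1.34.
- Median 20 months: 55-68%, 110-136 deaths, factor 1.45-1.40.

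**Reading B: the calendar date when the last patient reaches week 12.** Same formula with f = 2.77.

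- Median 9 months: 63-79% dead, factor 1.42-1.37.
- Median 20 months: 38-56% dead, factor 1.56-1.45.
- Share of patients treated at least 52 weeks earlier: (a + 2.77 − 12)/a = 62% to 81%.

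**Toxicity timing.** Nine months is 9/12 × 52 = 39 weeks. That lies beyond a 12-week assessment and inside a 52-week one.

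**The case against.** The strongest reply is that the sentence in 9.2 is loose writing. The trial's statistical decision is in section 9.5.2, the lower 95% confidence bound against −1 at 12 weeks, and nothing here touches it. In 9.2 the 12-week phrase is paired with a 4-week phrase in the next sentence, and both may be meant only to place the symptom result. Section 4.2 supports that reading. This is plausible, but the words of 9.2 attach 12 weeks to all the conditions, and three sections state one rule in different ways.

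A reader might infer stronger things that the documents do not support:

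- *That an early recommendation is planned.* No section schedules one. Section 9.6 plans no efficacy interim, and OS is assessed at LPLV. The rule permits early use of the data; it does not schedule it.
- *That most deaths would be missed.* This holds on reading A. On reading B, 38-79% of patients would already have died, and many would have passed 52 weeks.
- *That toxicity and quality of life contradict their definitions.* Both are defined at 12 weeks.
- *That arm A is known to carry the greater late risk.* The 9-month finding comes from 10 Gy fractions. The same section cites an 8 Gy regimen with acceptable toxicity, and section 6.1 gives normal-tissue equivalent doses of 17.6 or 35.2 Gy in arm A against 40 Gy in arm B.
- *That no method exists for judging comparability.* Section 9.5.1 sets 95% confidence intervals and section 9.5.3 includes Cox regression, so interval estimates are available. The criterion for comparable, and the weight of quality of life given that "Analyses of exploratory endpoints will be regarded as hypothesis-generating post-hoc analyses", can be left to the SAP.

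**Conclusion.** Wrong as written, of moderate severity. The OS condition in 9.2 conflicts with the only definition of OS in the protocol, the toxicity condition leaves out a planned secondary result, and sections 2.1 and 4.2 differ from 9.2. The primary analysis, error rate and sample size are unaffected. What is affected is what the trial may claim.

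The size depends on the reading. The loss of information is large if OS is cut at 12 weeks per patient: a hazard-ratio factor of about 1.9-2.5, against 1.34-1.45 at LPLV. On the calendar reading it is modest, with a factor of 1.37-1.56. These figures assume exponential survival and medians from two cited cohorts that need not match this population. The toxicity point does not depend on them: on 12 weeks of follow-up per patient, an effect that begins at 9 months cannot be observed.

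**What to change.** In section 9.2, limit 12 weeks to non-inferiority of the change in target-symptom intensity. Then state that the standard-of-care recommendation also requires the bladder and bowel toxicity results through 52 weeks and OS at LPLV, judged from the 95% confidence intervals of the arm difference and of the hazard ratio, not from a non-significant P value. Use the same wording in sections 2.1 and 4.2.

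The change is wording only and needs no new patients, visits or data. The downside is that the recommendation waits for data already planned. The 52-week comparison will also be limited by deaths: under the same survival assumptions 60% or 34% of patients (about 121 or 68 of 200) would have died by then, leaving about 79 to 132 before other losses. That is a further reason to report the interval.

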#### **2.1.4. Rationale for Timing of Endpoint Assessment**

In the PallRad study, assessment of symptom relief was performed at the end of treatment, and after 6 weeks and 12 weeks follow-up (primary endpoint) (8, 9). Results showed an increase in proportion of responders from end of treatment until 6 weeks, but the proportion was relatively stable between 6 and 12 weeks. The point in time of the expected maximum radiotherapy response depends, among other things, on the target symptom to be treated, and it can extend up to 12 weeks after treatment completion. To ensure correct assessment of all patients, including late responders, the primary endpoint will be assessed at 12 weeks. An additional assessment of symptom relief will be performed also after 26 weeks.

The pragmatic design of this study allows systemic cancer treatments in close proximity to the radiotherapy, which, for some patients, may interfere with the response assessment at 12 weeks. However, due to the randomized allocation of patients, and the total sample size, we expect this to be evenly distributed across the study arms.

The dynamics of the symptomatic response will provide relevant information, and it is therefore important to include early assessments at 4 weeks and 8 weeks as exploratory endpoints. In the PallRad study, patients were treated with a dose of 3 Gy per fraction. Due to the higher doses per fractions planned in this study (8 Gy in arm A, 5 Gy in arm B), we anticipate a more rapid symptomatic response. Furthermore, patients in arm A with unsatisfactory response will be offered a second radiotherapy fraction. From a radiobiological perspective, the interval between fractions should be kept at a certain minimum. Assessment of the symptom relief at 4 weeks (secondary endpoint) therefore represents a reasonable compromise between a reliable response evaluation and radiobiological considerations.

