## 4. Study Design

### 4.1. Overall Design

This is a prospective, randomized, open-label, national, parallel-arm non-inferiority phase III study designed to establish non-inferiority of radiotherapy with 1-2 fractions of 8 Gy to 5 fractions of 5 Gy (active comparator) with respect to patient-reported symptomatic relief. The study population includes patients with gastrointestinal, urological, or gynecological cancer considered as candidates for palliative radiotherapy due to symptomatic pelvic soft tissue tumors. Patients must have an expected survival beyond 12 weeks. Patients will be included over 2-4 years. Eligible patients identified in the screening period will be randomized to either arm A or arm B with an allocation ratio of 1:1 after collection of a signed informed consent. Study-specific baseline evaluation will be performed between date of signed informed consent and intervention start.

Patients in arm A will initially be treated with a single fraction of 8 Gy. In case of unsatisfactory symptom relief after 4 weeks of follow-up, a second radiotherapy fraction may be offered if at least one of the following two predefined criteria are met: 1)  $\leq 2$  point improvement on the NRS-scale and 2) initial symptomatic effect, but rapid deterioration ([Section 4.3.1](#)). Primary and secondary endpoints will be assessed after 4, 8, 12, 26 and 52 weeks of follow-up (last visit, toxicities only) after completed radiotherapy. Subjects will be followed with respect to overall survival until death or censoring (loss to follow-up, study withdrawal, or end of study).

The study timeline is presented in Figure 1.

[figure not shown]

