### **9.3. Sample size determination**

The sample size determination was based on a one-sided two-sample *t* test. The sample size estimation is based on the following assumptions:

- One-sided T-test with 2,5 % significance level (equivalent to a two-sided 95 % CI)
- Standard deviation (SD) of the primary endpoint equal to 2
- Non-inferiority margin (NIM) of 1

With these assumptions, we will reach a power of 85 % if we enroll 146 patients. Based on the PallRad study, we assume an exclusion from intention to treat (ITT) - population of around 25 % (8, 9), and we will need to randomize a total number of 200 patients.

This number of patients also provide sufficient power to claim non-inferiority on the exploratory endpoints defined in [Section 9.1](#). The exclusion from ITT set is expected to be lower at 4 weeks, increasing the statistical power of conclusions.

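### Sections 9.2 and 4.2 attach a treatment recommendation to a 4-week non-inferiority result that the protocol otherwise treats as exploratory and post hoc

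*Protocol*

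**What the plan says.** **The commitment.** Section 9.2 states: "If non-inferiority can be proven only 4 weeks after the intervention, a single fraction schedule will be recommend for patients". The group meant is those whose life expectancy is very short, provided such treatment is judged sensible for them. Section 4.2 says the same: "If non-inferiority can be proved only 4 weeks after completed radiotherapy, a single fraction schedule will be recommend".

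**Status of the 4-week endpoint.** The synopsis (1.1), Section 2.1.3 and Section 3 all place the 4-week change in target symptom among the exploratory items. Section 2.1.4 calls the 4- and 8-week assessments exploratory and then, in the same paragraph, writes: "Assessment of the symptom relief at 4 weeks (secondary endpoint) therefore represents a reasonable compromise". Section 9.5.4 says: "Analyses of exploratory endpoints will be regarded as hypothesis-generating post-hoc analyses".

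**Margin, rule and power.** Section 9.1 sets the margin of 1 NRS point for the 12-week change. Section 9.5.2 gives the confidence-interval rule for week 12. Section 9.3 adds: "This number of patients also provide sufficient power to claim non-inferiority on the exploratory endpoints defined in" Section 9.1, and notes that smaller losses at 4 weeks would raise power. Section 9.1 defines no exploratory endpoint.

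**Population.** Section 4.1: "Patients must have an expected survival beyond 12 weeks". Section 5.1 has the same criterion.

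**The concern.** An analysis cannot be both post hoc and the stated trigger for a recommendation. As written, week 12 and week 4 each open a route to a conclusion about practice, and the protocol neither orders the two tests nor shares a significance level between them.

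The word *only* in Section 9.2 can be read as *at 4 weeks but not at 12*, or as *as early as 4 weeks*. On either reading a recommendation rests on the exploratory result. On the first, it does so after the primary test has failed.

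The recommendation is also aimed at a group that the entry criterion was not written to enroll. Section 2 uses very short life expectancy for survival limited to a few weeks, while entry requires expected survival beyond 12 weeks.

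**Working it through.** **1. The plan's own figure.** Inputs from Section 9.3: one-sided level 2.5%, SD 2, margin 1, power 85%. Allocation is 1:1 (Section 4.1). A true difference of 0 is assumed, since the protocol does not state one.

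- Normal approximation: n per arm = 2 × SD² × (z₀.₉₇₅ + z₀.₈₅)² / margin² = 2 × 4 × (1.960 + 1.036)² / 1 = 71.8, so 72 per arm, 144 in total.
- Two-sample t test (noncentral t): 73 per arm, 146 in total, power 85.1%. This reproduces the stated 146.
- Loss of 25%: 146 / 0.75 = 194.7, so 195. The protocol plans 200.

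The sample size is therefore built on a single one-sided 2.5% test.

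**2. Two routes, each at 2.5%.** Suppose arm A is truly worse by exactly the margin at both times, and each time point is tested at one-sided 2.5%. With r the correlation between the two test statistics,

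P(at least one false finding) = 1 − Φ₂(1.96, 1.96; r).

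The documents give no r, so a range is shown. The last column subtracts the 2.5% of the week-12 test and is the chance of a false finding at week 4 alone.

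| assumed r | at least one false finding | week 4 alone |
|---|---|---|
| 0.3 | 4.76% | 2.26% |
| 0.5 | 4.54% | 2.04% |
| 0.7 | 4.17% | 1.67% |
| 0.8 | 3.90% | 1.40% |

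Independence (r = 0) gives 4.94%; r = 0.9 gives 3.52%.

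**3. What each remedy does to N.**

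- Week 4 hypothesis-generating, or tested only after week 12 succeeds: the familywise level stays at 2.5% and N stays at 146 evaluable, 200 randomized.
- Level split equally, 1.25% each, so that week 4 can stand alone: power at 146 falls from 85.1% to 77.4%. Regaining 85% needs 176 evaluable, and 176 / 0.75 = 234.7, about 235 randomized.

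**The case against.** The strongest defence is that the primary rule is untouched. The 2.5% in Section 9.3 is the level of the primary test, not a promised familywise rate, and Section 9.5.2 decides on week 12 alone. This stands. A reader might infer that the trial's stated type I error is breached, and the documents do not support that. The 3.9% to 4.8% is a worst case at the margin under assumed correlations. It counts non-inferiority findings, not recommendations: the 12-week recommendation in Section 9.2 also asks for comparable quality of life, toxicity and survival.

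Second, the two claims differ. The primary test concerns the strategy of one or two fractions. The 4-week result concerns a single fraction, because the second is offered only from the 4-week visit (Section 4.3.1). So it would be too strong to say that the very schedule that failed would be recommended. The second claim still has no error control.

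Third, it is an inference that the named patients are excluded. Section 9.2 puts no number on very short life expectancy, entry depends on *expected* survival, and Section 2 says clinicians overestimate it, so some enrolled patients may die early. What holds is that the recommendation extends beyond the entry criterion.

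Fourth, an SAP could add a testing order. It could not by itself remove a recommendation that the protocol commits to. The secondary label in Section 2.1.4 and the pointer to Section 9.1 may be slips, but they leave the endpoint's status unclear where it matters.

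A further reading is tempting. Section 9.2 also requires that "comparable QoL, toxicities and OS can be proved 12 weeks after the intervention", and a reader might infer that non-significant differences will be taken as proof. No passage says so. Section 4.2 says of superiority studies that fail to reject the null that "they should be interpreted as indeterminate". Sections 9.5.1 and 9.5.3 provide 95% confidence intervals and Cox regression, and week-52 toxicity is already a secondary endpoint. That argument is not part of this point.

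**Conclusion.** The contradiction is in the protocol text. Sections 9.2 and 4.2 promise a recommendation from a result that Sections 1.1, 2.1.3, 3 and 9.5.4 treat as exploratory and hypothesis-generating, without a margin or decision rule for week 4 and for patients beyond the entry criterion. The cost in error is at most moderate: 3.9% to 4.8% for at least one false finding against 2.5% for the primary test alone, of which 1.4 to 2.3 percentage points are week-4-only findings. This rests on both true differences lying at the margin, a level of 2.5% at each time, and an assumed correlation of 0.3 to 0.8. The primary analysis and its sample size remain sound. What needs correcting is the conclusion that may be drawn when only week 4 succeeds.

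**What to change.** - **Sections 9.2 and 4.2:** state that non-inferiority shown at week 4 but not at week 12 is hypothesis-generating and carries no recommendation. Limit any conclusion to patients like those enrolled, with expected survival over 12 weeks.
- **If a formal week-4 claim is wanted:** name the 4-week change in target symptom a key secondary non-inferiority endpoint, give it its own margin and analysis set, and test it only after week 12 succeeds.
- **Section 2.1.4:** use one label for the 4-week endpoint, matching Section 3 and the synopsis.
- **Section 9.3:** bring the sentence on power for exploratory endpoints into line with the chosen status. If week 4 becomes key secondary, name that endpoint and correct the pointer to Section 9.1. If it stays exploratory, remove the reference to claiming non-inferiority.

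The cost is protocol wording; N stays at 146 evaluable and 200 randomized. The downside is that no formal week-4 claim can be made if week 12 fails. Keeping that possibility through an equal split of the level would need about 235 randomized.
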